
### Outcome Measures

The primary outcome of the study is the medication dosage error rate in each allocation group during the sequence from drug preparation to drug injection. A secondary outcome is the elapsed time in seconds, in each allocation group, between the oral prescription by the physician and drug delivery by the nurse. TDP completion by the nurse is included in TDD. Comparisons of medication errors and TDD between allocation groups in each hospital and between each of the 6 hospitals will be assessed as secondary outcomes. At the end of the scenario, a 4-item questionnaire using a 10-point Likert scale will be provided to the participants. The questionnaire measures (1) the overall stress perceived (On a scale of 1 to 10, how much stress did you feel during the whole resuscitation scenario?), (2) the stress perceived with PedAMINES (On a scale of 1 to 10, how much stress did you feel using PedAMINES?), (3) the stress perceived with the infusion rate table (On a scale of 1 to 10, how much stress did you feel using the infusion rate table?), and (4) the satisfaction about the preparation method used during the resuscitation scenario (On a scale of 1 to 10, how much satisfaction did you get during the resuscitation scenario with the help of PedAMINES and with the help of the infusion rate table?). A baseline heart rate (HR) before the beginning of the scenario as well as continuous HR monitoring of each participant reflecting his or her stress level will be recorded during the resuscitation scenario. Mean delta HR values (difference between HR peak values and baseline HR) will be obtained during some small segments of scenario and correlated to the scenario phases and the preparation methods used. The segments of interest are (1) when prompted to start the resuscitation because of asystole just before massage and ventilation, (2) when prompted to prepare dopamine either with PedAMINES or the infusion rate table, (3) the first 30 seconds when dopamine is being prepared, (4) the last 30 seconds when dopamine is being prepared, (5) the setting up of the pump, (6) the washout period, (7) when prompted to prepare norepinephrine either with PedAMINES or the infusion rate table, (8) the first 30 seconds when norepinephrine is being prepared, (9) the last 30 seconds when norepinephrine is being prepared, (10) at announcement of successful resuscitation achievement, and (11) 1 minute later. Acceptability and usability testing of the app will be assessed using a 52-item questionnaire based on the unified theory of acceptance and use of technology (UTAUT) model [20]. UTAUT provides a useful tool to assess the likelihood of success for new technology introductions and helps to understand the drivers of its acceptance.

### Methods of Measurement and Data Collection

Final delivered drug concentration in μg/mL and infusion rate in μg/kg/min, TDP, and TDD will be collected during the scenario. All the actions (ie, primary and secondary outcomes) performed by the nurses during the scenario will be automatically recorded and stored by the responsive simulator detectors (Leardal SimJunior) and by 3 GoPro Hero 5 Black edition (GoPro Inc) video cameras. To avoid assessment bias, 2 evaluators will then independently review these video recordings. In case of disagreement, a third independent evaluator will help reach a consensus. The setup of the 3 cameras will be standardized to record at a resolution of 1080p, at 25 frames per second, wide field of view, and with a 16:9 aspect ratio. Cameras position will be standardized. The first camera will be placed in a harness on the nurse’s chest with an inclination of 10° downwards to film the front scene. The second camera will be placed on a tripod in front of the nurse, slightly above the head height, with an inclination of 90° downwards to film the bench where the drugs will be prepared. The third camera will be placed on a tripod 1 meter away from the nurse on his or her left (if right-handed) or right (if left-handed) and at the level of the navel to film the scene on the side. All actions performed with PedAMINES will be automatically saved locally in log files for further analysis. The validity and reliability of the app has been assessed in a prior study [14]. Stress level of each participant will be recorded during the entire resuscitation scenario with the HR monitor on a Polar A360 watch (Polar Electro Oy). The data will be stored on the wristwatch itself with further analysis being accomplished offline. Data collection will be carried out using Excel spreadsheet version 2011 (Microsoft Corp).

This study offers the great advantage of being very short in duration, around 30 minutes per nurse. Therefore, neither follow-up nor retention plans will be necessary. The intervention protocol is highly standardized, and nurse deviation from protocol in terms of drug preparation is a parameter that is of interest in our study (ie, in terms of medication errors or delays in drug preparation).

### Sample Size

The primary objective of this study is to detect a difference in rates of medication errors between groups (with PedAMINES vs without PedAMINES). In our crossover pilot study conducted in a single university hospital, the rate of medication errors was 70% (14/20, 95% CI 46%-88%) without PedAMINES and 0% (0/20, 95% CI 0%-17%) with PedAMINES [14]. We aim to reproduce these results in 3 university hospitals and 3 smaller hospitals. The sample size was calculated to have a power of 90% to detect a difference of at least 30% in rates of medication error between intervention groups in both sets of hospitals (university and smaller hospitals). We consider that a difference of 30% in the rate of medication errors is sufficient to modify the practice. We assumed a rate of error of 15% with PedAMINES and 45% without PedAMINES. Since this study is a crossover, observations will be paired and a McNemar test will be used to compare the rate of errors between intervention groups. For the sample size calculation, we assumed that 5% of nurses will commit a medication error with PedAMINES but not without PedAMINES and that 35% of nurses will commit a medication error without PedAMINES but not with PedAMINES (Multimedia Appendix 2). With a 2-sided risk alpha of 0.05, the needed sample size is 43 nurses for each set of hospitals. Finally, 8 nurses per randomized group must be recruited in each participating center (16 nurses per center). To prevent a potential loss of power due to misspecification of assumptions, 10 nurses will be recruited per randomized group and per participating center (total sample size: 120 nurses).

### Randomization and Blinding

Nurses will be randomized using a stratified, single, constant 1:1 allocation ratio determined with Web-based software [21]. Blinding to the purpose of the study during recruitment will be maintained to minimize preparation bias. Nurses will be unblinded after randomization. Allocation concealment will be ensured with sealed envelopes and will not be released until the nurses start the scenario. The study team members will be revealed just before the scenario starts, and videoreviewing will be done without blinding by both video reviewers but independently and blindly from one another.

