### Statistical Analysis

#### Primary Outcome

The rate of medication errors is the proportion of nurses committing a medication error. The rate of medication errors will be reported with 95% CI (Clopper-Pearson method) with each method and by study period to investigate a potential carryover effect. The error rates for each method will be compared using McNemar test for paired data. Differences in error rates will be reported with 95% CIs. Potentially, the efficacy of PedAMINES can be different according to the first method used in the crossover design (PedAMINES first: group A or the conventional preparation method first: group B). To investigate this potential effect, the difference in error rates (PedAMINES vs conventional method) will also be reported by randomized group (paired observations) and by period (independent observations). McNemar, chi-square, or Fisher exact test will be used to compare interventions. Errors will also be measured as the deviation in percent from the amount of delivered drug compared with the original dose prescribed by the physician. Absolute deviation will be analyzed. The mean (SD) difference in deviation obtained with each method will be reported with 95% CI. A *t* test for paired data will be used to compare interventions. Mean differences will be also reported by randomized group and by crossover period. We will assess the model for the presence of carryover and period effects following the Hills-Armitage approach to crossover study analysis [22]. The analysis of the primary outcome will be conducted for the university hospitals and for smaller hospitals.

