#### Secondary Outcomes

For TDD and TDP, the mean times will be reported with 95% CI for each arm and each study period to investigate a potential carryover effect. In case of a carryover effect, intervention arms will be compared within each study period using *t* tests for independent groups. If no carryover effect is found, data will be paired and analyzed using *t* tests for paired data.

For the primary and secondary outcomes, logistic regression analyses will be conducted to test a difference in rates of errors between university hospitals and smaller hospitals with PedAMINES and with the conventional preparation method. In a generalized estimating equation logistic regression model, an interaction between interventions and university/smaller hospitals will be tested to investigate a potential modification of the efficacy of PedAMINES in smaller hospitals compared with university hospitals. Analyses of primary and secondary outcomes will be conducted in nurses with more than 10 years of experience and in nurses with less than 10 years of experience. Means and standard deviations will be determined for stress and satisfaction scores of individuals for each questionnaire item as well as for the UTAUT questionnaire and reported with descriptive statistics. Pearson correlations will be computed between the HR measures obtained with the watch and the scenario phases for each of the preparation methods used. Data analysis will be carried out using GraphPad Prism version 6.0 (GraphPad Software, Inc) for graph figures, Stata/IC version 14 (StataCorp LLC) for descriptive analyses, and R version 2.15.2 (R Foundation) for statistical tests and 95% CI. Due to the nature of the interventions, we expect to have no missing data. In case of missing data, a complete case analysis will be conducted and no multiple imputation is planned. In order to assess interrater reliability on video reviewing, a kappa score—which provides a measure of interrater agreement independent of chance—will be calculated.

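### Allocation is balanced within each centre, but the between-nurse comparisons of the two methods ignore centre and are therefore mildly conservative

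*Protocol article*

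**What the plan says.** **Allocation.** Randomization and Blinding: "Nurses will be randomized using a stratified, single, constant 1:1 allocation ratio determined with Web-based software". The factor is not named. Sample Size adds that "10 nurses will be recruited per randomized group and per participating center". With six centres, that gives 20 nurses per centre and 120 in all. The caption of Figure 1 describes the flow per study centre. Centre as the stratum is an inference from these places. The equal group sizes within each centre are stated outright.

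**Within-nurse analyses.** Each nurse uses both methods. The main comparison of error rates is a McNemar test, and dose deviations are compared with a paired t test. TDD and TDP are compared with a paired t test if no carryover is found.

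**Between-nurse comparisons of the two methods.** There are two, and neither has a centre term:

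- Error rates by period, which the Primary Outcome section treats as independent observations: "McNemar, chi-square, or Fisher exact test will be used to compare interventions". McNemar serves the paired part, so the by-period part falls to chi-square or Fisher.
- TDD and TDP if carryover is found: "intervention arms will be compared within each study period using" t tests for independent groups (Secondary Outcomes).

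**The concern.** Within one period, nurses using the app are compared with different nurses using the infusion table. Because every centre supplies 10 nurses to each side, a centre that performs well or badly shifts both sides equally, and the shift drops out of the difference. The unstratified tests nevertheless compute their standard error from the total variance, centre differences included. The standard error is then too large, the interval too wide and the test less sensitive than the design allows.

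Centre differences are plausible on the article's own account. The Introduction expects marked disparities among nurses who see few paediatric resuscitations, and the centres run from university departments to smaller hospitals. At stake is some precision in the analyses that would carry the result if carryover or an order effect made the paired comparison doubtful.

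**Working it through.** **1. The plan's own figure.** Sample Size aims for "power of 90% to detect a difference of at least 30% in rates of medication error between intervention groups in both sets of hospitals". It adds: "We assumed a rate of error of 15% with PedAMINES and 45% without PedAMINES". The discordant proportions there are 35% (error without the app only) and 5% (error with the app only). With d = 0.35 − 0.05 = 0.30 and s = 0.35 + 0.05 = 0.40, the usual McNemar formula gives:

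n = [1.96 × √s + 1.2816 × √(s − d²)]² / d² = [1.96 × √0.40 + 1.2816 × √0.31]² / 0.09 = 42.39, rounded up to 43.

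This agrees with the article: "With a 2-sided risk alpha of 0.05, the needed sample size is 43 nurses for each set of hospitals". Spread over 3 centres × 2 groups, 43/6 = 7.17, rounded up to 8. Taking 10 instead gives 60 per set and 120 in total. The calculation is for a paired test in which each nurse is her own control, so the average level of a centre cancels. Nothing below changes it.

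**2. Effect of leaving centre out of a between-nurse test.** Let ρ be the share of outcome variance that lies between centres. The article gives no value, so ρ is assumed. With equal groups within each centre, the difference varies only with the within-centre part, (1 − ρ) × total variance, while the unstratified test uses the total. Hence:

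- ratio of reported to true interval width: k = 1/√(1 − ρ)
- actual size of the nominal 5% test: 2 × P(Z > 1.96k)
- power when a centre-adjusted test would have 80%: Φ(1.96 + 0.8416 − 1.96k)

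| ρ (assumed) | k | Interval too wide by | Actual size | Power (80% if adjusted) |
|---|---|---|---|---|
| 5% | 1.026 | 2.6% | 4.4% | 79% |
| 7.5% | 1.040 | 4.0% | 4.2% | 78% |
| 10% | 1.054 | 5.4% | 3.9% | 77% |

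**3. What a share of 7.5% looks like.** Suppose the table error rates in the six centres were evenly spaced from 25% to 65%: 25, 33, 41, 49, 57 and 65%. The mean is 45%, the article's assumed rate. The between-centre variance is 2 × (20² + 12² + 4²)/6 = 186.7 squared percentage points, or 0.0187. The total variance is 0.45 × 0.55 = 0.2475, and 0.0187/0.2475 = 7.5%. So 7.5% already stands for a wide spread between hospitals.

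If only the table rate varied and the app rate stayed at 15% in every centre, the total would be 0.2475 + 0.15 × 0.85 = 0.375 and the within-centre part 0.375 − 0.0187 = 0.3563. Then k = √(0.375/0.3563) = 1.026, so intervals are 2.6% too wide and power is about 79%.

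**4. Check by simulation.** Centre error rates were drawn at random around 45% for six centres, with 10 nurses per group in each, and 8,000 runs per setting. The unstratified test rejected in 4.7% of runs at ρ = 5% and 4.3% at ρ = 10%, against 5.4% at ρ = 0. The direction agrees with the table. The sizes are slightly milder, partly because six sampled centres show on average only 5/6 of the assumed between-centre variance.

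**The case against.** The case for leaving the plan alone is reasonable, and much of it stands.

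- **The main result is untouched.** McNemar and the paired t tests are within nurse. This stands in full. A reader might infer that the primary test is invalid or that 120 nurses are too few, but the article supports neither.
- **The analyses concerned are secondary in role.** By-period error rates are reported in addition, to look for an order effect, and the independent t tests apply only after a carryover finding. The error is on the cautious side and cannot create a false benefit for the app. This stands, and it limits the weight of the point.
- **Power may be ample anyway.** At 15% versus 45%, a chi-square test of 60 against 60 nurses has power Φ[(0.30 − 1.96 × √(0.42/60)) / √(0.375/60)] = 96%. That pools all six hospitals. The article also analyses each hospital set separately, and with 30 against 30 the same formula gives 73%. A small loss is not wholly idle there.
- **Some allowance is already made.** Separate analyses for university and smaller hospitals remove the difference between the two types, and comparisons within each hospital condition on centre. This stands in part: centres within a set can still differ, and the pooled by-period tests remain unadjusted.
- **The stratum is not named.** True, but the argument needs only the equal numbers per centre, which are stated.

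Two stronger readings are tempting. First, Outcome Measures says comparisons "between each of the 6 hospitals will be assessed as secondary outcomes", and a reader might infer 15 unadjusted pairwise hospital tests. No section prescribes pairwise testing, a single overall test fits the wording equally well, and the method may sit in an analysis plan that is not shown. Second, a reader might infer that ignoring centre inflates false positives. For the randomised comparison of methods it does the reverse. The university-versus-smaller contrast is not randomised and is a different question. Inflation there would depend on an assumed centre correlation and on inference beyond these six hospitals, and the article states neither.

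**Conclusion.** The point holds as a minor one about efficiency. The design balances the groups within centre, and the two stated between-nurse comparisons of the methods do not use that balance. For between-centre shares of 5% to 10%, intervals are about 3% to 5% too wide, the nominal 5% test runs at about 4.4% to 3.9%, and one to three points of power are lost from 80%. These sizes rest on the assumed shares, on the normal approximation and on equal group sizes within centre being achieved as planned. The direction, conservative, depends only on the balance and on some real difference between centres. The primary comparison, the paired analyses and the sample size stand as written.

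**What to change.** - State that centre is the stratification factor, if that is so.
- For error rates by period, replace the plain chi-square or Fisher test with a Cochran-Mantel-Haenszel test stratified by centre, and report a centre-stratified risk difference with its 95% CI.
- For TDD and TDP within a period, replace the two-sample t test with a linear model containing method and centre as fixed factors.
- Keep the McNemar and paired t tests as they are.

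The cost is a few sentences of analysis text and five degrees of freedom for six centres (two within a set of three). No extra nurses or data are needed, because centre is known for every participant.

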### Statistical Analysis

#### Primary Outcome

The rate of medication errors is the proportion of nurses committing a medication error. The rate of medication errors will be reported with 95% CI (Clopper-Pearson method) with each method and by study period to investigate a potential carryover effect. The error rates for each method will be compared using McNemar test for paired data. Differences in error rates will be reported with 95% CIs. Potentially, the efficacy of PedAMINES can be different according to the first method used in the crossover design (PedAMINES first: group A or the conventional preparation method first: group B). To investigate this potential effect, the difference in error rates (PedAMINES vs conventional method) will also be reported by randomized group (paired observations) and by period (independent observations). McNemar, chi-square, or Fisher exact test will be used to compare interventions. Errors will also be measured as the deviation in percent from the amount of delivered drug compared with the original dose prescribed by the physician. Absolute deviation will be analyzed. The mean (SD) difference in deviation obtained with each method will be reported with 95% CI. A *t* test for paired data will be used to compare interventions. Mean differences will be also reported by randomized group and by crossover period. We will assess the model for the presence of carryover and period effects following the Hills-Armitage approach to crossover study analysis [22]. The analysis of the primary outcome will be conducted for the university hospitals and for smaller hospitals.

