**Methods:**

This is a multicenter, prospective, randomized controlled crossover trial with 2 parallel groups comparing PedAMINES with a conventional and internationally used drug infusion rate table in the preparation of continuous drug infusion. The evaluation setting uses a simulation-based pediatric CPR cardiac arrest scenario with a high-fidelity manikin. The study involving 120 certified nurses (sample size) will take place in the resuscitation rooms of 3 tertiary pediatric emergency departments and 3 smaller hospitals. After epinephrine-induced return of spontaneous circulation, nurses will be asked to prepare a continuous infusion of dopamine using either PedAMINES (intervention group) or the infusion table (control group) and then prepare a continuous infusion of norepinephrine by crossing the procedure. The primary outcome is the medication dosage error rate. The secondary outcome is the time in seconds elapsed since the oral prescription by the physician to drug delivery by the nurse in each allocation group. TDD includes TDP. Stress level during the resuscitation scenario will be assessed for each participant by questionnaire and recorded by the heart rate monitor of a fitness watch. The study is formatted according to the Consolidated Standards of Reporting Trials Statement for Randomized Controlled Trials of Electronic and Mobile Health Applications and Online TeleHealth (CONSORT-EHEALTH) and the Reporting Guidelines for Health Care Simulation Research.

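### Drug and period are the same factor, so method differences within a randomized group cannot show an order effect, and the paired t tests for deviation, TDD and TDP should be period-adjusted

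*Protocol article*

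**What the plan says.** The Abstract (Methods) fixes the order of the drugs. Every nurse makes up dopamine first, by the allocated method, "and then prepare a continuous infusion of norepinephrine by crossing the procedure". Only the method is crossed.

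Under Statistical Analysis, Primary Outcome:

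- The main test pools both groups and has no period term: "The error rates for each method will be compared using McNemar test for paired data".
- The plan raises the possibility that efficacy differs with the method used first, and then says "To investigate this potential effect, the difference in error rates (PedAMINES vs conventional method) will also be reported by randomized group (paired observations". The sentence goes on to add the same difference by period, on independent observations. McNemar, chi-square or Fisher tests are named for these comparisons.
- Percent deviation from the prescribed dose is compared by a paired t test. "Mean differences will be also reported by randomized group and by crossover period".
- The presence of carryover and period effects is to be assessed by the Hills-Armitage approach. No period-adjusted estimate is named, and no consequence of finding a period effect is given.

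Under Secondary Outcomes, TDD and TDP are compared by a paired t test if no carryover is found, and within each period otherwise. The choice depends on carryover alone.

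**The concern.** In a two-period crossover, a difference between periods pushes the two within-group method differences in opposite directions. Here the period difference contains any difference in difficulty between two drugs, plus any learning within one short scenario. It need not be small, and the article gives no figure for it.

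Two consequences follow. First, the by-group results may show a large app effect in one group and a small one in the other when the method effect is identical in both. They are offered as evidence on the order question, so they could be taken for an order effect. Second, a paired test that ignores the groups leaves the period difference in its error term, so its intervals are too wide and its power is reduced.

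**Working it through.** **Inputs.** From Sample Size: error rates of 15% with the app and 45% without; discordant proportions 0.05 and 0.35; two-sided alpha 0.05; 90% power; 10 nurses per randomized group per center, hence 30 per group (60 nurses) in each set of three hospitals. The drug/period effect is not in the article and is assumed throughout, equal for both methods.

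**The plan's own figure.** With total discordance 0.40 and difference 0.30:

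n = [1.960·√0.40 + 1.282·√(0.40 − 0.30²)]² / 0.30² = (1.240 + 0.714)² / 0.09 = 42.4, rounded up to 43.

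This reproduces the article: "With a 2-sided risk alpha of 0.05, the needed sample size is 43 nurses for each set of hospitals".

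**What each contrast estimates.** Let m be the method effect (app minus table), p the drug/period effect (second minus first), and cA and cB the carryovers into period 2 in group A (app first) and group B (table first).

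- Within group A: m − p − cA
- Within group B: m + p + cB
- Gap between groups (B − A): 2p + cA + cB
- Period 1, between groups: m
- Period 2, between groups: m + cB − cA
- Gap between periods: cB − cA

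Dependence on order is the differential carryover, cB − cA. It appears in the gap between the by-period contrasts and does not appear in the gap between the by-group contrasts. An interaction of method with drug would also enter the by-period gap and cannot be separated from carryover.

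**Size for the error rate.** No carryover, 30-point method effect, 40% discordance, 30 nurses per group, at least 200,000 simulated trials per setting, uncorrected McNemar test:

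| Assumed drug/period effect | Group differences (points) | McNemar power in the two groups | Only one group significant |
|---|---|---|---|
| 0 | 30 and 30 | 79% and 79% | 33% |
| 10 points | 20 and 40 | 40% and about 100% | 60% |

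With no method effect and a 10-point drug/period effect, the within-group McNemar test at 30 per group rejects in 12% of trials at 40% discordance and in 22% at 20% discordance.

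**Precision, error rate.** At p = 10 points, the per-nurse variance is 0.40 − 0.30² = 0.31 unadjusted. Within groups it averages [(0.40 − 0.20²) + (0.40 − 0.40²)]/2 = (0.36 + 0.24)/2 = 0.30. The ratio is 0.31/0.30 = 1.033. Simulated power with 60 nurses is 98.7% for the pooled McNemar test and 99.0% for the period-adjusted estimate.

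**Precision, deviation, TDD and TDP.** Let s be the SD of the within-nurse difference inside a group. The unadjusted variance is larger by the factor 1 + (p/s)². With 60 nurses and an assumed method effect of 0.4 s:

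| p/s | Variance factor | Power, paired t | Power, period-adjusted t | Actual size of paired t at nominal 5% |
|---|---|---|---|---|
| 0 | 1.00 | 86% | 86% | 5.0% |
| 0.5 | 1.25 | 80% | 86% | 2.9% |
| 1 | 2.00 | 60% | 86% | 0.6% |

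The adjusted test keeps its 5% size throughout. With a method effect of 0.8 s, the paired t test has power above 99% in every row.

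**The case against.** The strongest reply is that the plan already holds the right contrast. It reports method differences by period, where both groups prepare the same drug, and it assesses period effects. This stands: the drug difference is looked for, and the order question can be answered from planned output. The plan nevertheless offers by-group and by-period results for the same question, with tests for both, and does not say that the by-group ones contain the drug effect.

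A reader might go further and infer that the by-group gap tells nothing about carryover. That is too strong. The gap contains the sum of the two carryovers, but mixed with twice the drug/period effect, so it cannot be interpreted rather than being empty. Nor does the article commit its authors to calling such a gap an order effect; it says only that the differences will be reported.

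A reader might also infer that the main comparison is biased or underpowered. The documents do not support this. Allocation is 1:1 with equal group sizes planned in each center, so the drug/period effect cancels in the pooled difference. The McNemar test errs only toward caution, and at the design alternative its power stays well above the 90% target.

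Finally, the Introduction describes large reductions in TDP and TDD in the pilot. If the method effect on times is 0.8 SD or more, the unadjusted paired t test loses almost no power. Its intervals are still wider than they need to be.

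**Conclusion.** The point holds as a correction to the order analysis and to the paired t tests, not as a fault in the primary test. Because drug equals period, method differences within a randomized group cannot show whether efficacy depends on the first method. With an assumed 10-point drug/period effect and no carryover, the two group tests disagree in about 60% of trials, against a baseline of 33% from sampling alone.

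For the error rate, the cost of leaving out period is about 0.3 of a power point at 10 points. For deviation, TDD and TDP, it ranges from almost nothing to a drop from 86% to 60%, depending on two quantities that the article does not give: the drug/period effect and the method effect, each relative to the within-nurse SD.

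**What to change.** In the Primary Outcome and Secondary Outcomes sections of the Statistical Analysis:

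1. For deviation, TDD and TDP, make the period-adjusted Hills-Armitage estimate the main analysis: the average of the two group-specific mean within-nurse differences, with the variance taken within groups.
2. Report by-group differences descriptively, without significance tests, and say that they contain the drug/period effect.
3. Use the planned by-period contrasts for the order question. State that drug cannot be separated from period, nor carryover from a method-by-drug interaction.
4. Keep McNemar as the primary test. A risk difference stratified by randomized group, or a Mainland-Gart test, beside it is optional.

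The cost is a change of wording and one degree of freedom. The randomized group is already known for every nurse, and no further data or participants are needed.
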